Emerging evidence suggests that brief case management interventions are effective in reducing the gap between institutional and community-based care and improving continuity of care (Susser et al, 1997; Dixon et al, 2009). When continuity of care and treatment gaps are addressed, individuals with serious mental illness and/or chronic physical conditions experience improved health outcomes that are also associated with reduced hospital and community costs (Adair et al, 2005; Mitton et al, 2005; Cabana & Jee, 2004; Saultz & Lochner, 2005; Gill & Mainous, 1998; Gill et al, 2000). Similarly, both experimental and non-experimental studies support the effectiveness of case management interventions in decreasing ED visits and hospitalizations for frequent users of EDs (Shumway et al, 2009, Althaus et al, 2011). In a large before and after program evaluation of case management interventions for frequent users of EDs in 6 counties in California, a decrease of 30% in ED visits and 17% in hospital costs was achieved one year after program enrolment. Findings in year 2 of the program demonstrated further improvements, with an estimated decrease in ED visits of 60%, inpatient days of 62% and hospital costs of 62% (Linkins et al, 2008). Experimental studies have provided further support for the effectiveness of case management interventions (Althaus, 2011). A randomized controlled trial of 252 frequent users by Shumway confirmed significant reductions in ED use and ED costs 12 months after enrolment in a case management program. The intervention also led to significant decreases in homelessness and alcohol use and improvements in accessing income support and health cards (Shumway, 2008). A recent systematic review by Althaus concluded that it may be beneficial to patients and economically justifiable for hospitals to implement case management for frequent users (Althaus, 2011).

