In determining a sample size calculation, three important factors were considered: 1) participants are eligible by being at the extreme of the distribution of emergency visits in the overall population and hence regression to the mean may play an important role in any observed change over time, 2) accessing emergency services may in fact provide a treatment that may contribute to change over time in an 'untreated' group, 3) previous studies have found that emergency visits tend to follow a negative binomial distribution (a count distribution with highly right skewed data), and 4) a proportional reduction in the rate of emergency department visits is the desired primary measure of impact of this intervention. To account for these factors, published data of Shumway et. al. (2008) was used to estimate the distribution of emergency department (ED) visits in an untreated group and its natural reduction over time; their study of frequent ED users (>5 visits/year) included a ‘usual care’ group and reported the mean and standard deviation of ED visits over 2 years of follow-up in 6 month blocks. The sample size calculation was performed using the formula derived by Toshiro Tango (Statistics and Probability Letters 79 (2009) 466-472) which uses a Poisson type outcome and assumes a random effect for each individual, which can accommodate a negative binomial or other more dispersed distribution. This approach also takes into account any fixed effects that covariates may have in both the pre and post-intervention period. Ultimately, this sample size calculation proposes that a sample size of 64 in each arm would allow the detection of a 20% reduction in ED visit rates (the minimum clinically significant difference we would like to be able to demonstrate). Since up to 30% attrition is expected, among participants, the final sample size will be 166 participants, 83 in each arm.

*Randomization process*

Participants will be recruited among successive referrals from participating TC-LHIN Hospitals. Participants able to provide capable informed consent will be invited to participate to the study. A research coordinator or research assistant will obtain written informed consent and complete a baseline interview prior to randomization to CATCH-ED vs. treatment as usual. Randomization will be allocated through the web-based electronic case report forms (eCRFs.) The randomization sequence will be generated by random computerized sequence in variable block sizes.

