**Analysis Plan**

We will calculate descriptive statistics (mean, standard deviation, quartiles) and construct graphs (histograms, scatter plots, box-plots) to characterize the clients at baseline with respect to socio-demographic factors, housing status, health status, and health service use. Baseline group comparisons will be conducted using chi-square test or Fisher’s exact test (for categorical variables), t-test or Wilcoxon rank-sum test (for continuous variables). We will construct plots to describe longitudinal changes in primary and secondary outcomes over time. All analyses will use an intent-to-treat perspective and will be compared with a per-protocol analysis. The primary outcome evaluates the proportional change in rate of emergency department visits (ED visits) between pre-intervention and 6-month time intervals post-intervention; some secondary outcomes (number of hospitalizations, days in hospital) are also count measures, negative binomial outcomes will be compared with Poisson regression accounting for overdispersion to determine the overall treatment effect. While it is usually customary to match the sample size calculation technique to analysis approach, in this case insufficient published data is available to calculate a sample size for a marginal techniques (Generalized Estimating Equations - GEE) that is proposed as our primary analytic technique. While GEE models represent the main question being studied (the impact of the intervention on population measures of ED use), conditional models can also provide useful information and sample size techniques require fewer assumptions. For this reason, both marginal and conditional (random effects models) will be fit and compared during the data analysis phase of this study. The choice of the most appropriate representation of the overdispersion of data (Negative binomial versus the use of an overdispersion factor in a poisson regression) is highly dependent on the variance structure observed in the collected data (Ver Hoef & Boveng, 2007); hence, the covariance estimates of the observed data will inform final model selection. GEE and mixed effects models will be compared to account for the repeated measurement of participants. A literature review and the presence of clinically significant differences in baseline data will determine which, if any, covariates require adjustment in the final model, and these will be included as covariates in the generalized linear regression models. Other secondary normally distributed outcomes (quality of life, service satisfaction) with be analysed using linear regression using the same principles of adjustment for clinically important covariates, and marginal versus conditional approaches.

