
Given the possibility of missing data in following participants for 12 months who may have unstable housing or community connections, imputation methods will be used to estimate the overall impact of missing data on outcomes. Administrative data from the Institute of Clinical and Evaluative will be used for the purposes of evaluating the primary outcome, and comparing the impact of missing data on outcomes.

*Economic Evaluation Plan*

The objective of the economic evaluation is to compare the cost-effectiveness of the CATCH-ED intervention with usual care, using patient-level data from the randomized clinical trial and linked administrative data at the Institute for Clinical Evaluative Sciences (ICES), Toronto. The Ontario MOHLTC perspective will be used in the analysis. In Ontario, the Ministry pays for physician visits, laboratory tests, imaging, hospitalization, emergency department visits, same day surgery/ procedure, complex continuing care and some home care services. In addition, the Ministry pays for prescription drugs for those older than 65 years old, live in a Long-Term Care Home or a Home for Special Care or enrolled in special programs such as the Ontario Disability Support Plan (ODSP). The time horizon for the economic evaluation will be 12 months (maximum follow-up of the trial).

The primary outcome will be the incremental cost per quality-adjusted life-year (QALY) gained though the intervention compared with usual care. The secondary outcomes include the incremental cost per ED visit avoided and incremental cost per hospital-day avoided.

Measuring QALYs: A QALY is a year of life experienced with a particular health-related quality of life (HRQoL) or health state utility, as represented on a scale from 0 to 1, where 0=death and 1=full health. The EQ-5D and SF-6D (converted from SF-12), generic preference-based instruments that have been used in mental health patients, will be used to assess patients’ health state utility at baseline, 6 months and 1 year. We will calculate each patient’s QALY from the utility scores using the area-under-the-curve approach, with linear interpolation between assessment points (Figure 1).

[figure not shown]

QALY0-90 days

QALY6 -12 months

QALY0-6 months

Figure 1. Calculating QALYs from EQ-5D utility scores

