Measuring resource use and costs: We will obtain the health care costs of each patient from linked administrative data at ICES (Table 1). Informed consent will be collected from each participant for linking study data to the administrative data at ICES. The two dataset will be linked using patients’ OHIP numbers.

Table 1. Data source

| **Resources** | **Sources** | **Variables** |
| --- | --- | --- |
| Hospitalization | Discharge Abstract Database | Cost estimated using Resource Intensity Weight (RIW) and cost per weighted case |
| Outpatient laboratory / imaging services and physician services (including inpatient, office and undefined service) | Ontario Health Insurance Plan (OHIP) Claims Database | OHIP billing cost estimated using utilization frequency of each service and cost per visit from OHIP fee schedule |
| Emergency Room visits / Same Day Surgery or procedure | National Ambulatory Care Reporting System (NACRS) and Same Day Surgery | Cost estimated using RIW and cost per weighted case |
| Outpatient prescription drugs | Ontario Drug Benefit Plan (ODB) | Drug cost and dispensing fee |
| Home care services | Home Care Database | Utilization frequency for each type of home care service |
| Complex continuing care | Continuing Care Reporting System | Case-mix index and duration between events or RWPD |

RWPD: RUG Weighted Patient Day is calculated by multiplying the case-mix index (CMI) and number of days for a particular RUG event. It accounts for admissions, assessments, re-entries, discharges, etc.

Calculating incremental cost per QALY gained: We will estimate average and incremental costs and QALYs for each group using multiple regressions:

[figure not shown]

[figure not shown]

where x is a vector of patient characteristics (e.g., age, sex), U­0 is the utility at baseline,10 TX­ is a treatment variable (TX=1 for intervention group), and the regression estimates β1 is the incremental cost and α1 is the incremental QALY.

Calculating incremental cost per ED visit avoided: We will estimate average and incremental costs (excluding ED visit costs) for each group using multiple regressions. The incremental cost per ED visit avoided is the incremental cost divided by the incremental number of ED presentations (more details in the statistical analysis section).

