Calculating incremental cost per hospital-day avoided: We will estimate average and incremental costs (excluding hospitalization costs) for each group using multiple regressions. The incremental cost per hospital-day avoided is the incremental cost divided by the average number of hospital-days (more details in the statistical analysis section).

Calculating net benefit regression: A treatment is cost-effective if the ICER is less than what the decision maker is willing to pay (λ) for the extra benefit (QALY gained, ED visit avoided or hospital-day avoided):

∆C/∆E <λ

We can also express this decision in terms of incremental net benefit, ∆NB:

∆NB = λ ∆E - ∆C

A treatment is cost-effective if it has a positive ∆NB, the value of the intervention’s extra benefits outweighs its extra costs. It is easier to estimate confidence interval for ∆NB because it is not a ratio. We will estimate the incremental net benefit of the intervention (β1) using multiple regressions:

NB= β0 + β1TX + β**X**

We could identify subgroups for whom the intervention is especially cost-effective using interaction terms. We will conduct net benefit regression analysis using different values of λ and will represent uncertainty using cost-effectiveness acceptability curves.

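### The cost per hospital-day avoided is defined with an average number of days as its denominator instead of the between-arm difference, so it is not an incremental ratio

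*Protocol*

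**What the plan says.** All the relevant text is in the protocol's Analysis Plan, under the Economic Evaluation Plan.

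- Status of the measure: "The secondary outcomes include the incremental cost per ED visit avoided and incremental cost per hospital-day avoided".
- Hospital-day ratio, numerator: "We will estimate average and incremental costs (excluding hospitalization costs) for each group using multiple regressions".
- Hospital-day ratio, denominator: "The incremental cost per hospital-day avoided is the incremental cost divided by the average number of hospital-days". The sentence does not say whether the average is that of usual care, of CATCH-ED or of both arms together. It refers the reader to the statistical analysis section for detail.
- ED-visit ratio, the parallel definition: "The incremental cost per ED visit avoided is the incremental cost divided by the incremental number of ED presentations".
- Decision rule, stated directly after the hospital-day ratio: the intervention is cost-effective if ∆C/∆E is "less than what the decision maker is willing to pay (λ) for the extra benefit (QALY gained, ED visit avoided or hospital-day avoided"). It is then re-expressed as ∆NB = λ∆E − ∆C and estimated by regression on treatment.

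**The concern.** A cost per day avoided needs the number of days avoided, which is the difference in mean hospital-days between the arms. The mean number of days spent in hospital is positive whenever anyone is admitted, and it does not show whether CATCH-ED avoided any of them. The ratio defined this way is a cost per day used, reported under the label of a cost per day avoided. Because the particular mean is not named, two analysts could also follow the sentence and report different values.

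At stake is one named secondary economic outcome. An analyst working from the sentence alone would report a figure that cannot be set beside the ED-visit ratio and that still looks like an ordinary cost per day avoided when the intervention avoided none.

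**Working it through.** The plan gives no numerical value for this ratio, so there is no figure to reproduce. The check compares the definitions and then works out by algebra how far the written ratio lies from an incremental one.

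**Definitions side by side**

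| Place in the Economic Evaluation Plan | Denominator |
|---|---|
| Cost per ED visit avoided | incremental number of ED presentations |
| Cost per hospital-day avoided | average number of hospital-days |
| General rule, with hospital-day avoided named as an effect | ∆E |

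The second row is the odd one out. The cross-reference does not settle it. The main Analysis Plan describes the primary outcome as a "proportional change in rate of emergency department visits" and lists days in hospital among the count outcomes to be modelled, but it gives no denominator for this ratio.

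**Inputs**

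- c = mean 12-month hospital-days under usual care. Not given in the protocol; it cancels from the factors below.
- r = proportional reduction in hospital-days under CATCH-ED. Not given for this trial, so a range is used. Three values are borrowed from the protocol. The first is 20%, from the sample size section ("a sample size of 64 in each arm would allow the detection of a 20% reduction in ED visit rates"), which concerns ED visits. The second is 30%, the one-year fall in ED visits in the before-and-after programme described in the Background. The third is 62%, that programme's year-2 fall in inpatient days ("with an estimated decrease in ED visits of 60%, inpatient days of 62% and hospital costs of 62"%), the only inpatient-day reduction the protocol quotes.
- ∆C = incremental cost excluding hospitalization. Not given; it also cancels from the factors.

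**Formulas**

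The CATCH-ED mean is c(1 − r), so days avoided are c − c(1 − r) = rc. The incremental ratio is ∆C/(rc). The factor by which it exceeds the written ratio is (average used)/(rc):

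- usual-care mean: c/(rc) = 1/r
- mean over both arms (equal size, 83 per arm planned): c(1 − r/2)/(rc) = (1 − r/2)/r
- CATCH-ED mean: c(1 − r)/(rc) = (1 − r)/r

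**Results**

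| r | usual-care mean | pooled mean | CATCH-ED mean |
|---|---|---|---|
| 10% | 10.0 | 9.5 | 9.0 |
| 20% | 5.0 | 4.5 | 4.0 |
| 30% | 3.3 | 2.8 | 2.3 |
| 50% | 2.0 | 1.5 | 1.0 |
| 62% | 1.6 | 1.1 | 0.6 |

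For example, at 20%: 1/0.20 = 5.0; 0.90/0.20 = 4.5; 0.80/0.20 = 4.0. At 62%: 1/0.62 = 1.6; 0.69/0.62 = 1.1; 0.38/0.62 = 0.6. A factor below 1 means that the written ratio is larger in magnitude than the incremental one.

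**Loss of sign** (assumed for illustration only: ∆C = 1,000, c = 10 days)

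| r | CATCH-ED mean | As written: usual-care / pooled mean | Incremental ratio |
|---|---|---|---|
| 20% | 8 | 1000/10 = 100; 1000/9 = 111 | 1000/2 = 500 |
| 0% | 10 | 100; 100 | undefined (no day avoided) |
| −20% | 12 | 1000/10 = 100; 1000/11 = 91 | 1000/(−2) = −500 |

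In the last row CATCH-ED costs more and adds hospital-days. The negative sign of the incremental ratio signals this; the written ratio does not, and barely moves across the three rows.

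**The case against.** The strongest reply is that this is a slip of one word. The outcome is named as a cost per day avoided, the ED-visit ratio is defined correctly, the general rule is ∆C/∆E, and the preceding sentence speaks of average and incremental costs, so the wrong adjective could easily have been carried over. That is a fair guess at what was meant. It does not remove the defect, because the sentence is the only place where this ratio is defined and it defines a different quantity.

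Three stronger readings are tempting, and the protocol does not support them.

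- A reader might infer that the ratio will always come out several-fold too small. That holds for modest reductions, but at 62% the factor is only 1.6 or 1.1, and with the CATCH-ED mean it is 0.6, in the other direction. It also presumes ∆C > 0. The protocol hopes for lower health care costs; if ∆C were negative with days avoided, a factor above 1 would mean that the written ratio understates the saving, and the correction would look more favourable.
- A reader might infer that the cost-effectiveness decision would be reversed. The rule against λ uses ∆C/∆E, and inference is by ∆NB and acceptability curves. None of these uses the average number of days, and the cost per QALY does not involve it.
- A reader might infer that the ED-visit ratio is also defective because the planned count models yield ratios of rates. Its denominator is correctly stated. How an absolute difference is obtained is a detail that a statistical analysis plan can settle.

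**Conclusion.** The definition is wrong as written and inconsistent with the rest of the Economic Evaluation Plan. Its clearest consequence needs no assumption about the size of the effect: as long as anyone is hospitalised, the formula returns a finite value whether or not days are avoided, and its sign carries no information about the effect on days. The numerical discrepancy when days do fall cannot be fixed from the protocol. It depends on the assumed r and on which average is taken, and whether correction looks better or worse depends on the sign of ∆C.

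The reach is narrow: the reported point ratio of one secondary economic outcome. It deserves correction before analysis, but it does not threaten the trial's primary outcome or its main economic conclusion.

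**What to change.** In the paragraph on the cost per hospital-day avoided, replace the average number of hospital-days as denominator with the between-arm difference in mean 12-month hospital-days per participant (usual care minus CATCH-ED). This matches the ED-visit ratio and the ∆C/∆E rule.

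The cost is one sentence and no new data. The reported ratio may become less favourable to the intervention. Like any incremental ratio, it will be unstable if the difference in days is close to zero; the net-benefit regression already planned avoids that problem.

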**Potential Impact:**

In Ontario, access, coordination and timeliness of appropriate services have been identified as health system goals (Ministry of Health and Long Term Care, 1999). Frequent users of EDs, poorly connected to community-based services, are at high degree of repeated ED visits and poor health outcomes. Given the potential for adverse consequences and associated health care costs, it is important for health treatment systems and providers to develop and implement strategies to increase community-based treatment engagement for this group and contribute to health system effectiveness and cost-effectiveness. Grounded on evidence-supported clinical interventions, CATCH-ED has the potential to substantially decrease ED visits, health care costs, as well as improve the patient experience, communication across providers and sectors, and health and social outcomes for some of the most vulnerable people in our community. The model promotes integration of hospital, primary care and community mental health services and can be implemented in a variety of settings across the province, including medium and smaller size cities, with little new investment. It is aligned with a number of Ontario MOHLTC priorities, including the ED Wait Time Strategy, and the Access to Family Health Care for All, as it aims to reduce ED wait times by reducing ED visits and readmissions to hospital as well as connect high risk clients to primary care physicians and specialists and improve care transitions across sectors and between health providers.
